The complete analysis dataset will consist of all the anemic patients with no missing values for any parameters in the dataset. The primary variables include MCHC, MCV, RDW, and MCHC. All the data will be summarized for the PBS and automated hematology analyzer results of the anemic patients. Demographic variables will be presented using frequencies and percentages for categorical data and means and standard deviations for continuous data. Outcome variables for continuous data will be analyzed and summarized with maximum, mean, minimum, standard deviation, standard error, and a 95% confidence interval for parametric data. Continuous outcome variables will first be tested for normality using the Kolmogorov-Smirnov test at a 5% significance level (p≤0.05). To compare the results of CBC and PBF methods, data will be evaluated finding the sensitivity, specificity, positive predictive value (PPV), negative predictive value (NPV), and accuracy for both methods. If the data is normally distributed, a paired t-test will compare the means of related groups (CBC group with positive and negative cases). If the data is not normally distributed, the Mann-Whitney test will be used. However, the PBS group with positive and negative cases will be evaluated using the chi-squared test or McNemar's test. This analysis will determine the more effective diagnostic method.

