## Results

This study therefore seeks to determine whether an RBC histogram can diagnose the three types of anemia, microcytic, macrocytic, and normocytic [15], with reference to the traditional method of diagnosing the condition using the PBS examination. This study will determine the efficiency of RBC histogram analysis by comparing the diagnostic findings with that of PBS examination which will be used. Thus, the use of this approach will offer the researcher an understanding of how efficient RBC histogram analysis is as compared to the PBS examination in the identification of diverse types of anemia. Better results in diagnostic capabilities are expected, with RBC histograms likely providing more precise and quantifiable data on RBC indices. Implementing RBC histogram analysis in routine clinical practice is expected to enhance diagnostic processes for anemia, leading to a more effective and timelier patient treatment.

Table 1 shows the metric table to compare the RBC histogram and PBS.

**Table 1 TAB1:** Metric table to compare the RBC histogram and PBS RBC: red blood cell; PBS: peripheral blood smear; PPV: positive predictive value; NPV: negative predictive value

Metric	RBC histogram	PBS
Sensitivity		
Specificity		
PPV		
NPV		
Diagnostic efficiency (overall accuracy)		
Time per sample		
Cost per test		

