The PBS examination is crucial for diagnosing hematological disorders like anemia. Despite its accuracy, manual PBS analysis remains tedious, error-prone, time-consuming, and reliant on skilled laboratorians. While manual microscopic evaluation is the gold standard for PBS analysis, an automated system is crucial for quicker, more accurate diagnosis. The review highlights the need for a large, annotated PBS dataset and a robust system to handle staining and imaging variations. A hybrid method combining morphological and clinical features could enhance anemia classification efficiency [4]. This study examined the relationship between RBC histograms from the Abbott Cell-Dyn Ruby analyzer and PBS results in 500 blood samples. Dimorphic anemia cases showed normal MCV, MCH, and MCHC, with increased RDW due to anisocytosis and poikilocytosis. Macrocytic anemia cases had elevated MCV, MCH, and RDW with normal MCHC. The study concluded that histograms complement PBS in diagnosing RBC disorders and reliably correlate with PS interpretations in anemia cases [17]. In another study of 354 adult blood samples with Hb <10 mg/dl, RBC histograms and PBS were compared to classify anemia into four types. The majority of cases were normocytic, with histograms showing high sensitivity for normocytic and macrocytic anemia but low specificity. Microcytic anemia had higher specificity but lower sensitivity. Overall, histograms were effective for detecting normocytic and microcytic anemia. Discordance in macrocytic anemia was noted due to histograms detecting subtle morphological changes not visible under light microscopy [18]. This study expects that the integration approach of these two diagnostic procedures will give a broader view and understanding of anemia. Clinicians get a greater accuracy by the cross-verification of results of RBC histograms and indices with PBS findings. For example, automated analysis can quickly and accurately look through and differentiate between the types of anemia, and PBS can then offer confirmation of the findings or point out the abnormalities that the automated system did not pick up on. Also, integrating RBC histogram analysis in the daily practice of diagnosis may reduce the time taken in diagnosis and increase the speed at which they are conducted. This can result in faster actions by the healthcare provider and improved care for the patient, as prompt identification of anemia is key to treating it. The study results are expected to provide valuable insights into the integration of these diagnostic tools, enabling them to function cohesively within a unified system. The identification of the analyzers offers remarkable precision, while the PBS provides detailed morphological insights [4].

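### The plan promises a verdict on which diagnostic method is better, but nothing it specifies can decide that verdict

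*Protocol article*

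**What the plan says.** All but the last two items below come from the Statistical analysis section of the protocol article (Materials and methods).

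- **Decision:** "This analysis will determine the more effective diagnostic method".
- **Primary variables:** "The primary variables include MCHC, MCV, RDW, and MCHC". That is four entries and three distinct variables.
- **Accuracy:** "data will be evaluated finding the sensitivity, specificity, positive predictive value (PPV), negative predictive value (NPV), and accuracy for both methods". No measure is ranked above another.
- **CBC test:** if the data are normal, "a paired t-test will compare the means of related groups (CBC group with positive and negative cases"; otherwise Mann-Whitney.
- **PBS test:** "the PBS group with positive and negative cases will be evaluated using the chi-squared test or McNemar's test".
- **Significance level:** in this section 5% appears only for the normality check ("tested for normality using the Kolmogorov-Smirnov test at a 5% significance level (p≤0.05"). The Sample size section uses 5% again, for a precision calculation.
- **Target and reference:** the Results section asks "whether an RBC histogram can diagnose the three types of anemia, microcytic, macrocytic, and normocytic", and words the smear examination as what the histogram is judged against.
- **Table 1:** rows for the five accuracy measures, time and cost; one column each for RBC histogram and PBS; no breakdown by anemia type.

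**The concern.** A verdict between two methods needs four things: a measure on which both are scored, a reference independent of both, a paired contrast of the two scores, and a rule that turns the result into a conclusion. The plan promises the verdict without fixing these. An analyst who followed it literally would have a set of index summaries, two sets of within-method tests and a filled-in Table 1, and would still have to decide what makes one method better.

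The study's comparative conclusion is at stake. It would either be fixed in advance by the choice of PBS as reference, or rest on a row or anemia type chosen once the data are known.

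**Working it through.** **1. Does the sample size identify a deciding contrast?** Inputs from the Sample size section: z = 1.96, p = 0.286, E = 0.05.

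n = z² × p × (1 − p) / E² = 3.8416 × 0.286 × 0.714 / 0.0025 = 313.8, rounded up to 314.

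The stated figure reproduces. It gives precision around an anemia prevalence and contains no difference between methods, so it does not show which comparison was meant to decide.

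**2. Can each specified element name a winner?**

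| Element | What it compares | Can it name CBC or PBS as better? |
|---|---|---|
| MCV, MCHC, RDW | Analyzer values | No. The described smear reading is morphological, with no matching index values |
| Paired t-test or Mann-Whitney | Positive against negative cases within CBC | No |
| Chi-squared or McNemar | Positive against negative cases within PBS | No, as worded |
| Five accuracy measures | Each method against a reference | Only with an independent reference, a ranked measure and a paired contrast; none is given |
| Time, cost | The two methods | Only on time or cost; no rule weighs them against accuracy |

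**3. If PBS is the reference.** For any anemia type, the PBS result and the reference are the same reading, so PBS has no false positives and no false negatives. Provided both positive and negative readings occur:

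- sensitivity = TP / (TP + 0) = 100%
- specificity = TN / (TN + 0) = 100%
- PPV, NPV and accuracy are likewise 100%.

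The histogram can at best tie. The accuracy comparison is settled before any data are collected.

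**4. If some other reference were used.** The measures need not agree. The counts below are assumed, for N = 314 (158 with the target type, 156 without).

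| | TP | FN | FP | TN | Sens. | Spec. | PPV | NPV | Accuracy |
|---|---|---|---|---|---|---|---|---|---|
| Method A | 150 | 8 | 40 | 116 | 94.9% | 74.4% | 78.9% | 93.5% | 84.7% |
| Method B | 135 | 23 | 15 | 141 | 85.4% | 90.4% | 90.0% | 86.0% | 87.9% |

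A leads on sensitivity and NPV; B leads on specificity, PPV and accuracy.

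A simulation took two truly equal methods (both assumed 85% accurate against an independent reference, three types, 314 patients). Somewhere among the 15 measure-by-type comparisons, the point estimates favored different methods in 83% to 86% of runs. Significant results in opposite directions occurred in only about 1% of runs.

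**5. Error rate, for illustration only.** Suppose three one-type-versus-rest McNemar tests, each at two-sided 5%, were run on 314 paired classifications with no true difference in type frequencies.

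- Large-sample value for three equally frequent types: the three contrasts sum to zero and correlate at −0.5. The chance that any |Z| exceeds 1.96 equals the chance that the range of three independent standard normals exceeds 1.96 × √2 = 2.77, which is 12.2%.
- Simulation with assumed type mixes of 50/40/10%, 60/30/10% and equal thirds, and 10% to 30% of patients typed differently by the two methods: 11.6% to 13.0%.

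The illustrative figure is therefore about 12%, against 5% for one test.

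**The case against.** **Deferral to the SAP.** A condensed article commonly leaves alpha allocation and test hierarchy to fuller documents that are not shown. This stands: a missing multiplicity adjustment is not a finding here. It does not cover the main point, because the article itself names the primary variables, the tests and the decision, and these do not fit together.

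**Uncontrolled false positives.** A reader might multiply five measures by three types and infer an inflated error rate over 15 tests. The documents do not support this. They never cross measures with types, Table 1 has no rows by type, and no between-method test of any accuracy measure is named. The 5% level belongs to the normality check and the sample size. Error on the three index variables is also beside the point, since a false positive there could not name a winner. The error rate is undefined; it cannot be shown to have a particular inflated value.

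**Either method could be declared the winner.** A reader might infer this too. With PBS as reference, as Results words it, PBS cannot lose on accuracy. With another reference, conflicting point estimates are likely, but significant results in opposite directions were rare.

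**The cited 354-sample study.** The Discussion reports "histograms showing high sensitivity for normocytic and macrocytic anemia but low specificity. Microcytic anemia had higher specificity but lower sensitivity". This might be read as evidence of conflicting verdicts. It describes one method's trade-off across types, not a disagreement over which of two methods is better.

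**A headline measure may exist.** Table 1 labels overall accuracy as diagnostic efficiency, and Results speaks of determining the histogram's efficiency. This is arguable, but the Statistical analysis section gives accuracy no priority, and the reference problem remains. The Abstract and Conclusions lean toward combined use of both methods, which is a further reason to drop the superiority sentence.

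**Conclusion.** The concern holds in a limited form. The plan claims that its analysis will settle which method is better, and no stated contrast can do so. If PBS is the reference, the accuracy verdict is predetermined. If it is not, the verdict would depend on a measure or anemia type that the plan does not choose. This conclusion rests on the text alone.

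The figures only illustrate it. The roughly 12% assumes three McNemar tests that the plan does not state. The conflicting-rows example uses assumed counts, and the 83% to 86% assumes equal 85% accuracy and an independent reference. None of them is an error rate of this plan. The data to be collected are unaffected; the fault lies in the conclusion the plan says it will draw, and a change of text repairs it.

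**What to change.** 1. Delete the last sentence of the Statistical analysis section. This is necessary because agreement statistics cannot say which method is better.
2. Name one primary analysis: the per-patient 3x3 table of anemia type by histogram and indices against type by smear, reported as percent agreement and kappa, each with a 95% CI. Optionally add one Stuart-Maxwell test at two-sided 5% for systematic differences in type assignment.
3. Make the following secondary, with 95% CIs where applicable and no claim that either method is better: per-type sensitivity, specificity, PPV and NPV of the histogram against PBS; the index summaries; time and cost. Label Table 1 accordingly.

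**Cost.** A few sentences and a table label; no added patients, samples or readers. With 314 complete pairs, the 95% CI half-width for percent agreement is at most 1.96 × √(0.25 / 314) = 5.5 percentage points, and 1.96 × √(0.85 × 0.15 / 314) = 3.9 points if agreement were 85% (assumed). The small downside is that the study reports agreement and can no longer declare a winner.

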## Abstract

Background

Anemia is characterized by a lower red blood cell (RBC) count than the usual rate or the average count that should be found in the blood. It is described by the reduction in the concentration of hemoglobin, the number of RBCs, and the O2-carrying capacity of the blood. A complete blood count (CBC) gives serious information on changes in the size and shape of RBCs and an indication of inclusion bodies that will help exclude anemia. RBC indices suggest potential reasons for the anemia in a particular patient. Thus, RBC indices can give some clues about the possible cause of anemia in a given patient with the disease. It is also necessary to look at the peripheral blood smear (PBS) and RBC indices and histogram to evaluate anemia adequately.

Method

The primary complaints of volunteers, such as clinical anemia as well as essential family medical history, will be the criteria for selection. After that, the main procedures that will be performed are the PBS and CBC. The blood sample will be drawn while the individual sits securely and in an aseptic setting. An ethylenediaminetetraacetic acid (EDTA) tube will be used to collect 2 ml of venous blood, which will then be gently mixed and processed on a five-part automated hematology analyzer (Coulter) for CBC test and PBS.

Expected results

The diagnostic capabilities of the PBS procedure are expected to match with RBC histograms and indices in the CBC report for the detection of anemia. Comparing both results with the PBS evaluated at the microscopic assessment, it is expected to likely provide a more precise and quantifiable result on RBC morphology and indices with greater accuracy for anemia detection in accordance with the PBS report. Implementing RBC histogram analysis in routine clinical practice is expected to enhance the diagnostic processes for anemia, leading to a more effective and timelier patient treatment.

Conclusion

These findings will suggest that applying RBC histograms and indices in CBC reports in supportive diagnosis with PBS analysis in the everyday clinical practice of hematology may improve the diagnoses and overall care of patients with anemia. Advanced research should confirm the efficacy of integrated approaches to increase diagnostic accuracy.

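### Accuracy metrics are planned for both the analyser and the smear with no independent reference named, so they cannot show which method is more effective

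*Protocol article*

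**What the plan says.** The Statistical analysis section lists the metrics to be estimated, ending with "negative predictive value (NPV), and accuracy for both methods". It closes with the decision to be drawn from them: "This analysis will determine the more effective diagnostic method".

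The Results section states the aim as whether the histogram can diagnose microcytic, macrocytic and normocytic anemia "with reference to the traditional method of diagnosing the condition using the PBS examination". It adds: "This study will determine the efficiency of RBC histogram analysis by comparing the diagnostic findings with that of PBS examination". The Abstract likewise expects "greater accuracy for anemia detection in accordance with the PBS report".

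Table 1, introduced as the "metric table to compare the RBC histogram and PBS", has one column per method. Its rows are the five accuracy metrics, time per sample and cost per test. The article names no other diagnostic standard. Under Data collection procedure, a single EDTA sample serves both the analyser and the smear.

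**The concern.** Sensitivity and specificity need a truth that lies outside the test being scored. Here two tests are to be scored and ranked, and the only yardstick named is one of the two. A method scored against itself makes no errors, so its column carries no information. Every disagreement is charged to the other method, including disagreements in which the yardstick was wrong.

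The Discussion shows that this is not an idle worry. In summarising a cited study of 354 samples it reports: "Discordance in macrocytic anemia was noted due to histograms detecting subtle morphological changes not visible under light microscopy". In Table 1, with PBS as the reference, such patients would count as histogram errors. At stake is the study's comparative conclusion on diagnostic accuracy.

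**Working it through.** **The plan's own figures.** The article gives no figure for this comparison. Its one design figure, the sample size, reproduces: 1.96² × 0.286 × 0.714 / 0.05² = 313.8, hence 314. It rests on anemia prevalence and does not bear on this point.

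**Step 1: what Table 1 would contain.** Take one anemia type against the rest in n patients. Let a = both methods positive, b = analyser positive and PBS negative, c = analyser negative and PBS positive, d = both negative.

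| Metric | Analyser, PBS as reference | PBS, PBS as reference | Analyser, analyser as reference | PBS, analyser as reference |
|---|---|---|---|---|
| Sensitivity | a/(a+c) | 100% | 100% | a/(a+b) |
| Specificity | d/(b+d) | 100% | 100% | d/(c+d) |
| PPV | a/(a+b) | 100% | 100% | a/(a+c) |
| NPV | d/(c+d) | 100% | 100% | d/(b+d) |
| Accuracy | (a+d)/n | 100% | 100% | (a+d)/n |

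The accuracy gap is (b+c)/n in favour of whichever method serves as the reference. With perfect agreement (b = c = 0) the two tie.

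**Step 2: what a ranking needs.** When they disagree on a type, exactly one method is right. If the analyser is right in w of the b+c discordant patients, the true accuracy difference (analyser minus PBS) is [w − (b+c−w)]/n = (2w − b − c)/n. The count w can lie anywhere from 0 to b+c, and no data named in the article inform it.

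**Step 3: can anemia status serve as the truth?** Under Participants, everyone enrolled is already diagnosed with anemia. There are no non-anemic patients from whom to estimate specificity.

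**Step 4: illustration.** The accuracies below are assumptions; the documents give none. Let the analyser's true sensitivity and specificity both be 0.95 and those of PBS 0.90, with independent errors and PBS as the reference. For type share π:

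- Apparent sensitivity = [π·0.90·0.95 + (1−π)·0.10·0.05] / [π·0.90 + (1−π)·0.10]
- π = 0.5: (0.4275 + 0.0025)/0.50 = 86%; specificity is also 86%.
- π = 0.3: (0.2565 + 0.0035)/0.34 = 76.5%; specificity (0.5985 + 0.0015)/0.66 = 90.9%.
- Overall accuracy at any π: 0.95·0.90 + 0.05·0.10 = 86%, against 100% for PBS.

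The true difference is 0.95·0.10 − 0.05·0.90 = +5 points for the analyser; Table 1 would show −14. Swap the true values (analyser 0.90, PBS 0.95) and the true difference becomes −5, while Table 1 still shows −14.

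**Step 5: sensitivity to the assumptions.** With PBS at 0.85 and the analyser at 0.95, the analyser's apparent accuracy is 0.8075 + 0.0075 = 81.5%. Its apparent sensitivity is 57.8%, 76.2% and 85.5% at type shares of 20%, 40% and 60%, with specificity 91.2%, 85.5% and 76.2%. If instead every analyser error is also a PBS error (0.95 against 0.90, maximal overlap), agreement is 0.90 + 0.05 = 95%. The distortion shrinks, but PBS still scores 100%.

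**The case against.** The Statistical analysis section never designates PBS as the reference. The Results wording could be read as a plain head-to-head comparison, and planning accuracy for both methods itself suggests that PBS was not meant to be its own standard. This stands, and it limits the claim: a reader might infer that PBS wins by construction, but that holds only on the reading in which PBS is the reference. It does not rescue the plan, because the alternatives are a column with no defined truth or a contest that the analyser cannot lose.

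Other stronger readings are tempting and not supported:

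- **That the article declares PBS the gold standard for this study.** The Discussion says "manual microscopic evaluation is the gold standard for PBS analysis". It does so in summarising a cited review, where manual reading of smears is set against automated systems.
- **That the plan predicts a histogram more sensitive or specific than PBS.** The better results anticipated in the Results section are tied to quantifying RBC indices, and much of the article presents the methods as complementary.
- **That no third standard is collected.** Only a condensed article is at hand, and it does not describe how the entry diagnosis was made. The text supports only that none is named.
- **That no comparison at all is possible.** Time per sample and cost per test need no reference.

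It is also fair to say that the illustration assumes its accuracies, and that errors on a shared blood sample may be positively correlated, which would narrow the gap.

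**Conclusion.** The concern holds in this form: with no independent reference named, the five accuracy metrics cannot show which method is more effective. This is more than detail left to a fuller document, because the article itself states the metrics, the comparator, the table shell and the decision, and these do not fit together.

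That conclusion follows from the algebra and needs no assumed values. The reference method scores 100% and leads in accuracy by exactly the proportion of discordant patients. The sizes quoted (an apparent gap of 14 points, or 18.5 points with PBS at 85%) depend on the assumed accuracies and on independent errors. They show the direction and possible scale of the distortion and do not predict the result.

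**What to change.** 1. In Table 1, remove the five accuracy cells from the PBS column. Keep time per sample and cost per test for both methods.
2. For each anemia type, report the analyser's classification as sensitivity and specificity relative to PBS, or as positive and negative percent agreement. Add overall agreement with 95% confidence intervals; kappa is optional.
3. Replace the closing sentence of the Statistical analysis section with a statement that the analysis estimates how far the analyser's classification agrees with PBS. Align the conclusions on accuracy with it.
4. Keep the accuracy comparison of the two methods only if the full protocol already holds an independent reference diagnosis. In that case name it, apply it to both methods, and compare sensitivity and specificity in a paired analysis (McNemar). Without a reference, McNemar's test between the methods compares only how often each one calls a type.

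Items 1 to 3 need no new data. With 314 patients and, for example, 86% agreement, the 95% interval is about ±1.96 × √(0.86 × 0.14/314) = ±3.8 points. The cost is a narrower objective: the study would report agreement and could not declare one method the more accurate.
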